**2.2. Study variables**

The study variables are the socio-demographic characteristics age, sex, address, type and category of tuberculosis.

**2.3. Data collection techniques and tools**

All patients who are diagnosed to have TB will be asked to submit 5ml blood sample to the laboratory for routine lab investigations. The health worker in tuberculosis clinic will assign a unique study number to each patient on the data collection format. The laboratory technician will draw blood specimen by sterile technique using disposable needle, syringe and gloves. He or she will label the blood specimen with the same unique study number assigned by health worker in Tb clinic without any other identifier. They will keep the samples in a refrigerator with optimum temperature. The laboratory technician or health worker from TB clinic will transport the specimen in cold chain and deliver to the regional laboratory.

Laboratory technologists will conduct anonymous HIV testing according to the national HIV testing algorithm. They will register the results on the data collection format and submit to principal investigator.

**2.4. Sample size calculation**

n =

Where: n = the sample size

p = the proportion of pulmonary tuberculosis patients infected with HIV q = 1- p

z = the percentage level at 95% confidence interval (1.96) d = the margin of error = 2.5%

Study from the region showed that the prevalence of TB HIV co-infection rate of about 20%.[39]

Based on this

n = = 984

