**Study - V**

This is a cross-sectional study or survey to find the proportion of tuberculosis patients infected with human immunodeficiency virus. The investigator will select ten sites from the region as part of regional surveillance of HIV infection among tuberculosis patients. The study will include all tuberculosis patients diagnosed over six months period. Trained laboratory technicians and health workers from tuberculosis clinic /data collectors/ will administer pr-tested questionnaire and record socio-demographic variables as age, sex, residence, classification and category of tuberculosis. Tuberculosis patients will give serum for HIV testing. The laboratory technicians will label and store the blood specimen as per the recommendation for HIV testing. They will transport the specimen to regional reference laboratory under cold chain. Trained laboratory technologists in the regional reference laboratory will do HIV testing under national testing algorithm. The results will be anonymous and unlinked.

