**2.4. Sample size calculation**

Community based tuberculosis care reduced 30% of patient cost in health facility to 13 % in community-based tuberculosis treatment in a study conducted in Tanzania.[34] Based on this

n = [(z1 + z2)*2*P]/

n = the sample size from each district z1 =level of significance of 95 %( 1.96)

z2 =power of the study of 90 %( 1.28) p1 = patient cost in facility based tuberculosis treatment (30%)

p2 = patient cost in community-based tuberculosis treatment (13%)

P= the average proportion of treatment success in the control and intervention groups (21.5%)

n = = = 123

IF = 1 + (m-1)*ICC

IF - inflation factor or design effect m - number of cluster size 15 assuming equal cost per cluster

ICC - intracluster correlation coefficient assuming typical ICC of 0.04

IF = 1 + (m - 1)*ICC = 1 + (15 - 1) * 0.04 = 1.56

Effective sample size = IF * calculated size = 1.56* 123 = 192

In addition, the cost related to tuberculosis treatment supervisors, community health agents, tuberculosis programme coordinators in the district and health institution will be included.

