**2. Methods**

**2.1. Study design**

This is a cross-sectional study to find out the acceptability of community based tuberculosis care. The study will include all health workers (health professionals, health extension workers and community health agents), community members, and tuberculosis patients who completed their treatment (ex tuberculosis patients) in the study sites. Based on the sample size, study subjects will be randomly selected from all intervention clusters. Community members next to treated tuberculosis patients will be included in the study. Next fifth household on the right side of treated tuberculosis patients’ house will be included. Health workers working in tuberculosis clinic, health extension workers and tuberculosis treatment supervisors will be included in the study.

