**2. Methods**

**2.1. Study design**

This is a cross-sectional study/survey to find out the proportion of tuberculosis patients infected with HIV in the region. As part of regional tuberculosis and HIV infection, the investigator will select nine sites from the region. Selection criteria of the sites are that they should have laboratory technician, well performing DOTS programme, laboratory reagents, functional x-ray machine, functional refrigerator to store blood sample and be accessible for supervision. All tuberculosis 15 years old or more patients on treatment will be included in the study.

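### Study V's 2.5-point margin of error ignores clustering in nine or ten sites; the design supports about 3.5 to 5.8 points, and Study I has the same omission to a smaller degree

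*Protocol*

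**What the plan says.** Study Five, section 2.4, builds its sample size from three inputs:

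- the confidence level: "z = the percentage level at 95% confidence interval (1.96");
- the expected proportion: "Study from the region showed that the prevalence of TB HIV co-infection rate of about 20" per cent;
- the target precision: "d = the margin of error = 2.5" per cent.

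The result is 984. No inflation factor, ICC or remark on clustering appears.

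Study Five, section 2.1, sets out where the patients come from: "As part of regional tuberculosis and HIV infection, the investigator will select nine sites from the region". Section 6.2 (Study V) gives a different number: "The investigator will select ten sites from the region as part of regional surveillance of HIV infection among tuberculosis patients". Section 6.2 takes every patient diagnosed over six months. Section 2.1 states that the target is the co-infection proportion for the region, and that sites are selected on laboratory capacity, a well-performing DOTS programme, equipment and accessibility.

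Study One, section 2.4, uses the same kind of calculation (p = 20%, d = 5%, n = 246) for suspects found in the trial's intervention clusters. Study Four, section 2.4, does likewise (p = 64.5%, d = 5%, n = 351), but its subjects are sampled differently: "Based on the sample size, study subjects will be randomly selected from all intervention clusters".

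Studies Two and Three do allow for clustering. Both use IF = 1 + (m − 1) × ICC with "ICC - intracluster correlation coefficient assuming typical ICC of 0.04" and m = 15, which gives 1.56.

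**The concern.** A margin of error from a simple-random-sample formula holds only if patients are close to independent draws from the target population. Patients at one site share a catchment area, and HIV prevalence can differ between catchments. With about 100 patients per site and only nine or ten sites, even a small between-site correlation greatly reduces the effective sample size. The protocol makes this correction for units of 15 patients in Studies II and III and leaves it out for Study V, where the units are about seven times larger (109 / 15 ≈ 7).

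At stake is the precision promised for a regional HIV co-infection estimate. A reader would plan around 20% ± 2.5 points when the design can support only a materially wider interval.

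**Working it through.** **Step 1: reproduce the stated sizes.** The formula is n = z²pq/d² with z = 1.96.

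- Study V: 3.8416 × 0.20 × 0.80 / 0.025² = 983.4, stated 984.
- Study I: 3.8416 × 0.20 × 0.80 / 0.05² = 245.9, stated 246.
- Study IV: 3.8416 × 0.645 × 0.355 / 0.05² = 351.9, stated 351 (rounded down).

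All three therefore carry a design effect of 1.

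**Step 2: add clustering to Study V with the protocol's own factor.** m = 984/9 = 109.3 or 984/10 = 98.4. IF = 1 + (m − 1) × ICC. Half-width = 1.96 × √(0.20 × 0.80 × IF / 984). The values 0.01 and 0.02 are assumptions; 0.04 is borrowed from Studies II and III.

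| ICC | Sites | IF | Effective n (984/IF) | Half-width, points |
|---|---|---|---|---|
| 0.01 | 9 | 2.08 | 472 | 3.61 |
| 0.01 | 10 | 1.97 | 498 | 3.51 |
| 0.02 | 9 | 3.17 | 311 | 4.45 (4.448 before rounding, so 4.4 to one decimal) |
| 0.02 | 10 | 2.95 | 334 | 4.29 |
| 0.04 | 9 | 5.33 | 184 | 5.77 |
| 0.04 | 10 | 4.90 | 201 | 5.53 |

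Against 2.5, the interval is 1.4 times (3.5/2.5) to 2.3 times (5.8/2.5) as wide. At ICC 0.001 it is still 2.6 points.

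**Step 3: could more patients at the same sites recover 2.5 points?** With k sites, the half-width cannot fall below 1.96 × √(0.16 × ICC / k), however many patients are enrolled. Setting this equal to 0.025 gives ICC = k/983.4, which is 0.009 for nine sites and 0.010 for ten. Above that ICC, 2.5 points is out of reach at these sites.

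**Step 4: Study I.** Study Two, section 2.4, arrives at 17 clusters per group by one method and 14 by another. So m = 246/17 = 14.5 or 246/14 = 17.6. Half-width = 1.96 × √(0.16 × IF / 246).

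- ICC 0.01, 17 clusters: IF = 1.13, half-width 5.3 points.
- ICC 0.05, 14 clusters: IF = 1.83, half-width 6.8 points.

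The range is about 5.3 to 6.8 points against the stated 5, for an assumed ICC of 0.01 to 0.05.

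All these figures assume equal numbers per site or cluster and keep z = 1.96. A t multiplier on the eight or nine degrees of freedom that the Study V sites provide would widen its interval further.

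**The case against.** **The ICC is not known.** The 0.04 was assumed for treatment success in village clusters and reused for cost. It was not given for HIV status or for case yield among suspects. This stands, and it is why the result is a range. The direction does not depend on it: any positive ICC widens the interval, and Study V is well above 2.5 points at 0.01.

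**984 may be exceeded.** Taking all patients for six months could yield more than 984, and Study I could recruit more than 246. For Study I this could restore 5 points: at ICC 0.04, about 560 suspects in 17 clusters or 794 in 14. For Study V it does not help once the ICC passes about 0.01 (step 3).

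**Study IV.** A reader might infer that all three descriptive studies fail equally. The protocol does not support that. Study IV subjects are randomly selected within all the intervention clusters. If the conclusions stay with those clusters, this is close to stratified sampling and the loss may be small. Only inference beyond them would bring in a design effect. Interviewing neighbours of former patients could add some correlation, but that does not establish a shortfall of known size.

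**Reported intervals.** A reader might also infer that the published intervals will be too narrow. The document does not show this. Section 6.7 names only the software, and the interval method may be set elsewhere. What can be criticised is the planned margin.

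**Scope.** These are descriptive studies. The randomised comparison in Study II already carries a design effect and is not touched by this point. The Study I margin also refers to a detection proportion, so restating it says nothing about the precision of the tool's diagnostic value.

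**Conclusion.** The point holds for Study V. Its stated margin of 2.5 points is that of a simple random sample, and the design described does not deliver it for a regional estimate. The realistic half-width is about 3.5 to 5.8 points over an ICC of 0.01 to 0.04. This rests on an assumed ICC, roughly equal site sizes, and the region as the target, which the protocol states. The conflict between nine and ten sites is real but shifts the result by at most about 0.2 points.

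Study I has the same omission with a modest effect, from barely above 5 to just under 7 points. For Study IV no shortfall is established unless inference goes beyond the intervention clusters.

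Sites in Study V are chosen for performance, equipment and accessibility. A design effect deals with variance only. Even a correctly widened interval would not cover bias from that selection.

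**What to change.** 1. Reconcile the number of Study V sites between section 6.2 and Study Five, section 2.1.
2. In Study Five, section 2.4, restate the expected margin using the inflation factor of Studies II and III with a stated ICC range. For ICC 0.01 to 0.04 this is about 3.6 to 5.8 points with nine sites, or 3.5 to 5.5 with ten.
3. In Study One, section 2.4, give the margin as a range in the same way, about 5.3 to 6.8 points for ICC 0.01 to 0.05.
4. State that the Study V and Study I confidence intervals are computed with site or cluster as the sampling unit.
5. Add a sentence that Study V sites were chosen for performance and accessibility, so the interval does not reflect site-selection bias.
6. For Study IV, say whether conclusions are limited to the intervention clusters. If they are not, treat it as in items 3 and 4.

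The cost is a few rewritten lines and a cluster-based interval calculation. No extra patients or sites are required. Spreading Study V over more sites would improve precision, but it would need further staff, equipment and cold-chain transport, so it is not part of this fix.

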**TUBERCULOSIS SYMPTOM BASED SCREENING TOOL**

**Questionnaire no.________ Name of interviewer ______________________Date__________**

**1. Socio-demographic variables**

1.1 Name of suspect _______________________________ 1.2. Age_____1.3. Sex ___________

1.4. Cluster __________ Kebele ______________Residence urban _____ rural ______________

1.5. Marital status Single___________ Married_____________ Divorced________________

Widowed_______ other (specify) _________________________________

1.6. Educational status No schooling ______ Grade ______ other (specify) ________________

1.7. Occupation of suspect Farmer _________ student ________ merchant ________________

Housewife _________government employee________________________

daily labourer__________ others (specify) _________________________

**2. Tuberculosis symptoms and history**

|  | Tuberculosis symptoms and history | No | Yes | Duration in weeks |
| --- | --- | --- | --- | --- |
| 2.1. | Did you experience cough for two or more weeks? |  |  |  |
| 2.2 | Is the cough productive of sputum? |  |  |  |
| 2.3. | Does sputum contain blood? |  |  |  |
| 2.4. | Did you have fever? |  |  |  |
| 2.5. | Did you have loss of appetite? |  |  |  |
| 2.6. | Did you loss weight? |  |  |  |
| 2.7. | Did you have chest pain? |  |  |  |
| 2.8. | Did you have history of tuberculosis treatment? |  |  |  |
| 2.9. | Did you have closer contact with known tuberculosis patient? |  |  |  |

**COMMUNITY HEALTH WORKERS FIELD LAB REQUEST FORM**

**Unique number ________**

**Socio-demographic variables**

1. Name of TB suspect _________________________________ 2. Age________3. Sex _______

4. Cluster _______________ Kebele ______________________ Date ___________________

**Sputum specimen for microscopic examination**

**Sputum specimen sputum cup number slide number sputum result**

1st spot ___________ _________ ________

2nd morning ___________ ________ ________

3rd spot ___________ ________ ________

**Name of community health agent Name of laboratory technician**

**Signature Signature**

**LAB RESULT OF SPUTUM EXAMINATION IN YAH**

**Unique number ________**

**Socio-demographic variables**

1. Name of TB suspect _____________________________________ 2. Age_____3. Sex ______

4. Cluster _______________ Kebele ______________________ Date ___________________

**Sputum specimen for microscopic examination and culture**

**Sputum specimen sputum cup number FM result Bleach result culture result**

1st spot ______________ _________ ________ ___________

2nd morning _____________ _________ ________ ___________

3rd spot ________________ _________ ________ ___________

**Name of lab. technician - FM Name of lab. technician - bleach Name of lab. technician culture**

**Signature Signature Signature**

**Questionnaire: Community based tuberculosis treatment outcome**

**Identification**

1. District TB number ________________Unit TB number ____________

2. District_______Cluster number______Kebele _________Date_______

**Socio-demographic variables**

3. Age _______ 4. Sex: ____ 5. Residence urban ______ rural _______

6. Marital status Single _ Married _ Divorced _ Widowed _other (specify)_

7. Educational level No schooling __ Grade ____other (specify) ________

8. Occupation Farmer ________ student ________ merchant ________

Housewife _______government employee______________

Daily labourer_______ others (specify) ________________

**Patient follow up and treatment outcome**

1. Disease classification PTB+ve ______ PTB -ve ______ EPTB ________

2. Patient category New____ Relapse____ Failure_____ Defaulter______

Transfer in____ other (specify) _________________

3. Sputum smear results of PTB +ve patients

2nd month __________ 5th month _________ 7th month _______

4. Treatment outcome cured ___ treatment completed ___ died ______

Defaulted ____ failure ____ transfer out _______

Other (specify) ___________________________

**COMMUNITY BASED TUBERCULOSIS CARE – TB PATIENT FORM**

Questionnaire no.________ Name of interviewer __________ Date___________

**Socio-demographic variables**

1. Name of TB patient___________________ 2. Age________3. Sex _____

4. Cluster ________________ Kebele ___________ 5. Religion ______

6. Marital status Single___ Married___ Divorced___ Widowed____ other___

7. Educational status No schooling ____ Grade ____ other ________

8. Occupation of suspect Farmer ____ student ___ merchant ___others _

**Cost items for diagnosis for the patient**

1. number of travel days ____ travel expense per day ____travel hours__
2. expenses for food ________ drink _______ others with expense _____

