**6.2.** **Study design**

**Study - I**

This is a cross-sectional study to evaluate the diagnostic value and applicability of community based tuberculosis-screening tool in tuberculosis case finding. The investigator will select matched clusters and randomly allocate to intervention and non-intervention clusters. Community health agents from the intervention clusters will organize community mobilization sessions monthly and register patients with cough of two weeks or more. Then they will run the diagnostic tool. Patients with symptoms suggestive of pulmonary tuberculosis will give sputum specimen according to the recommendation of national tuberculosis guideline. The community health agent will keep the sputum specimen in a box prepared for this purpose and transport the sputum specimen, the same day, to diagnostic health institution for laboratory examination. Laboratory technicians will stain the sputum specimen using by Ziehl-Neelsen technique on the same day. Then they will do direct microscopic examination. They will make the results ready for the next day. In addition, they will send sputum specimen for fluorescent microscopy, bleach digestion technique and culture. Patients in the non-intervention clusters will continue the conventional self-reporting and investigation in diagnostic health facilities.

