**2.4. Sample size calculation**

The proportion of pulmonary tuberculosis cases detected by Sidama tuberculosis control programme is about 20%.

n =

Where: n = the sample size

p = the proportion of pulmonary tuberculosis patients detected

q = 1- p

z = the percentage level at 95% confidence interval (1.96)

d = the margin of error = 5%

Based on this

n = = 246

**STUDY TWO - TO ESTIMATE THE TREATMENT OUTCOME OF TUBERCULOSIS PATIENTS SUPERVISED BY COMMUNITY HEALTH AGENTS/ TREATMENT SUPERVISORS**

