**2. Methods**

**2.1. Study design**

This is a randomized controlled community trial to find out the costs per tuberculosis patient treated successfully in the intervention and non-intervention districts. Cost related to tuberculosis control programme in the study sites will be determined according to the actual expenses and time cost. Programme coordinators, health workers, community health agents, tuberculosis treatment supervisors, tuberculosis patients and relatives accompanying them to health facilities in the study sites will be included in the study.

The cost analysis will follow societal perspective to analyse the cost per patient. The data collectors will obtain financial reports from districts and health institutions finance sections to collect expenditures for tuberculosis control programme, health workers and community health agents’ time and costs associated to tuberculosis prevention and control activities. In addition, they will collect cost of the patient and the relative who accompanied them during their visit to health institutions.

The investigator will use cost per tuberculosis patient successfully treated as an outcome measure. Future cost and productivity gains will not be included in the study. Standard cost estimation of all expenses and time of the patient, treatment supervisor and health workers will be done. Data collectors will use a structured pre-tested questionnaire for data collection.

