**2.2. Study variables**

The study variables are the socio-demographic characteristics, time, cost incurred during tuberculosis case detection, follow up and treatment. In addition cost related to supervision and monitoring and evaluation of tuberculosis control programme in the study sites will be included.

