**Cost items for sputum collection**

1. number of hours spent per community education _________________
2. total number of days community mobilization conducted____________
3. total number of hours spent for sputum collection ________________
4. total number sputum collected per session ______________________
5. number of hours spent on sputum transportation _________________
6. number of days sputum is transported to health facilities ___________
7. number of hours spent for sputum result collection _______________

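### Study III records case-finding labour for all suspects but user diagnosis costs for confirmed patients only, so the cost comparison between arms depends on a cost left out of both

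*Protocol*

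**What the plan says.** The protocol's Study Three, section 2.1, sets the perspective: "The cost analysis will follow societal perspective to analyse the cost per patient". It also sets the outcome: "The investigator will use cost per tuberculosis patient successfully treated as an outcome measure". Section 2.2 puts case detection inside the costing, naming "time, cost incurred during tuberculosis case detection, follow up and treatment" among the variables.

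The people costed are listed in section 2.1. Besides programme staff, community agents and treatment supervisors, "tuberculosis patients and relatives accompanying them to health facilities in the study sites will be included in the study". Suspects are not named. The summary table of the individual studies also gives only health workers and TB patients as the population of the third study.

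The annexed forms follow that list. The only form with user-side diagnosis items is the TB patient form, in the block "Cost items for diagnosis for the patient" and a similar block for an accompanying relative. The community health worker form asks for education hours, mobilisation days, "total number of hours spent for sputum collection", hours spent transporting specimens and hours spent collecting results. None of these items is restricted to suspects who prove to have TB.

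On the route to diagnosis, section 6.2 (Study I) says: "Patients in the non-intervention clusters will continue the conventional self-reporting and investigation in diagnostic health facilities". In intervention clusters, Study One section 2.3 has the community worker collect all specimens and deliver them to the laboratory.

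**The concern.** Community sputum collection shifts work from the suspect, who would otherwise travel to a facility, to the community worker. A societal costing should treat both sides of that exchange alike. Here the worker's time is recorded whatever the smear result, while the travel it replaces is recorded only for suspects who turn out to be patients. Most people examined may test negative, so the missing part of user cost could be large relative to the recorded diagnosis cost.

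At stake is the between-arm difference in total cost per success. Part of it would reflect whose costs were collected, not what the two approaches cost. The costed participants and the forms are fixed in the protocol, so analysis cannot recover this cost unless suspect counts are deliberately brought in.

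**Working it through.** **The plan's own figure.** Study Three section 2.4 gives 123 per group, inflated to 192. With P = (0.30 + 0.13)/2 = 0.215, n = (1.96 + 1.28)² × 2 × 0.215 × 0.785 / 0.17² = 122.6, so 123. Then 1.56 × 123 = 191.9, so 192. The figure reproduces. It has no bearing on which costs are collected.

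**What the forms record for case finding.**

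| Resource | Intervention clusters | Control clusters |
|---|---|---|
| Community worker time | recorded, all suspects | does not arise |
| Laboratory time | form usable in both arms | form usable in both arms |
| User travel and time, confirmed patients | recorded | recorded |
| User travel and time, negative suspects | not recorded | not recorded |

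The last row is missing in both arms. The first row stands in for part of it in one arm only.

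**Illustration of the omitted user cost.** Let y be the share of examined suspects who are confirmed, c the user cost of one negative suspect, and s the treatment success proportion. Then

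omitted user cost per success = [(1 − y)/y] × c / s.

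Inputs:
- s = 0.70 (control) and 0.85 (intervention), from Study Two section 2.4.
- c = 1 unit for a control suspect's facility diagnosis and r units for a local community visit. The protocol gives neither, so r is varied.
- y is not given and is varied. The nearest figure is in Study One section 2.4: "The proportion of pulmonary tuberculosis cases detected by Sidama tuberculosis control programme is about 20" per cent. Reading it as yield among suspects is an assumption.

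Control arm:
- y = 0.10: 9/0.70 = 12.9 units omitted per success
- y = 0.20: 4/0.70 = 5.7 units
- y = 0.30: 2.33/0.70 = 3.3 units

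Intervention arm at y = 0.20: 4r/0.85 = 4.71r, which is 0 to 2.4 units for r from 0 to 0.5. The net omission then falls on the control arm, by 5.7 down to 3.4 units.

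**When the direction reverses.** The two omissions are equal at

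r* = {[(1 − y_C)/y_C]/0.70} / {[(1 − y_I)/y_I]/0.85}.

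- Equal yields: r* = 0.85/0.70 = 1.21
- y_C = 0.20, y_I = 0.10: 5.71/10.59 = 0.54
- y_C = 0.20, y_I = 0.05: 5.71/22.35 = 0.26

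Below r* the larger omission is in the control arm, which works against community care. Above r* it is in the intervention arm. For example, with y_C = 0.20, y_I = 0.05 and r = 0.5, the net is 5.71 − 11.18 = −5.5 units, the opposite direction.

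**The case against.** The strongest reply has four parts.

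- **How worker hours enter the numerator is not stated.** The worker form also asks how many specimens were collected per session, so hours could be apportioned per specimen and charged to confirmed patients alone. An analysis plan not seen here may settle this. This stands: the protocol shows that the hours are recorded for all suspects, not that they are charged in full. Charging them to confirmed patients only would make the arms more alike, but would drop part of the case-detection cost from a societal total.
- **Negative suspects in intervention clusters are uncosted too.** They attend a session, take a cup home and return the next day. This stands, and it is why the direction is not certain.
- **Intervention clusters also use facility diagnosis.** Study Two takes all diagnosed patients, and its outcome form includes smear-negative and extrapulmonary disease. This stands and narrows the contrast between arms.
- **Finance records cover the gap.** They do not. They show provider spending, not a suspect's travel or lost time.

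A reader might infer something stronger: that the result is simply biased against community care, with 80% of control diagnostic travel missed. That takes 1/0.20 = 5 suspects per case and 2 facility days each, so 10 days of which 2 are recorded. With 60 treatment visits, 62 of 70 user travel days would be counted, an 11% shortfall. The documents do not support these as findings. The 20% may be a case-detection proportion, the days field on the form is open, and the 60 visits are not in the protocol. On the same inputs, and reading the 30% in Study Three section 2.4 as the user share of total cost, the shortfall is 0.30 × 8/62 = 3.9% of counted control cost. That is small beside the 35% and 43% reductions cited in the literature review. It rests on the same unsupported inputs, so it does not show that the gap is negligible either.

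**Conclusion.** The point holds in a limited form. Study III claims a societal cost that includes case detection, yet it leaves out the travel and time of negative suspects in both arms while recording, for all suspects, the labour that replaces that travel in one arm. The comparison of total cost per success therefore depends on an omitted cost.

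The omission probably works against community care. The literature review expects patients' visits and costs to fall when community workers collect and transport sputum, section 6.1 describes diagnostic facilities as less accessible, and the worker carries the specimens. With equal yields, a local visit would have to cost more than 1.21 times a facility visit to reverse this. At intervention yields of 10% or 5% against 20% in control, 0.54 or 0.26 of a facility visit is enough. These break-even values rest on the planned success rates and on assumed yields. The size of the effect cannot be computed from the protocol. This is a worthwhile, inexpensive improvement, not a flaw that invalidates the study.

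**What to change.** 1. Report treatment and follow-up cost per patient treated successfully separately from case-finding cost, and base the supervision comparison on the former. The patient, laboratory and community worker forms already hold diagnosis and treatment items in separate blocks. District supervision and finance-report costs are not split this way and need a stated allocation rule.
2. For the total including case finding, where suspect counts by cluster can be obtained from the community request forms and laboratory registers, multiply user-side diagnosis cost per confirmed patient by suspects examined per confirmed case, in both arms. Show a sensitivity range for yield and for cost per negative suspect.
3. Where counts cannot be obtained, state that the costs of negative suspects are excluded and that the total comparison is limited by this. The community request form carries the cluster, but the protocol does not say that facility registers do so for self-reporting suspects, so control counts may not be retrievable.

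The first step costs almost nothing. The second needs some extra counting and assumes that negative suspects spend about as much per diagnostic visit as confirmed patients.
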